## Methods/design

### Study design

The proposed study is a prospective, multicenter, double-blind, randomized controlled, (methylprednisolone versus placebo) phase-III superiority trial performed on two parallel groups. The primary objective is to evaluate the efficacy of corticosteroid treatment in patients with CSDH without clinical or radiological signs of severity. Secondary objectives are to assess the effect of methylprednisolone on quality of life evolution, morbidity and mortality, and radiological evolution of the lesions. This trial is registered at ClinicalTrials.gov as NCT02650609. This article has been written following the Standard Protocol Items: Recommendations for Interventional Trials (SPIRIT) guidelines [27] (Additional file 1).

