### Study population

Our hypothesis is that 80% of the patients taking placebo will be operated on at 1 month. A total sample size of at least 202 patients (142 events) is required to achieve 90% power to detect a decrease in the rate of surgery to 60% (hazard ratio of 1.756) with methylprednisolone, using a two-sided log-rank test with a 0.05 significance level assuming that the hazards are proportional (nTerim, V1.1, Statistical Solutions Ltd., Cork, Ireland).

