#### Analysis of the primary endpoint

Time to surgical treatment (i.e., the delay of occurrence of surgical treatment) of the CSDH at 1 month will be compared between the two groups with the log-rank test. Two interim analyses after inclusion of one third and two thirds of the patients, and one final analysis are planned. Stopping rules will use the alpha spending function with the O’Brien-Fleming boundary. The cumulative values of alpha for each analysis are: 0.00021 at the first analysis, 0.01202 at the second analysis and 0.04626 at the final analysis (nTerim, V4.0, Statistical Solutions Ltd., Cork, Ireland). The trial will be stopped early if the significance of the log-rank test is below these alpha values.

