### Data Safety Monitoring Board

An independent Data and Safety Monitoring Board is constituted before study initiation and comprises five members who are not involved in the study, including a neurosurgeon, a neurologist, an endocrinologist, a pharmacologist and a methodologist. The Data and Safety Monitoring Board meets after each interim analysis and at the end of the study. It can also meet on the request of the coordinating investigator or the methodologist if serious adverse events, or results which can jeopardize the existence of the protocol, occur. The Data and Safety Monitoring Board can propose to stop the study if interim statistical analyses reach significance or if it appears that study continuation would be contrary to ethics rules for safety reasons, or if the publication of trial results yields data that proves our hypothesis.

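### The statistical section makes an efficacy stop mandatory on the 1-month surgery test alone, while the monitoring board section makes it a proposal; the two rules conflict and must be reconciled

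*Protocol article*

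**What the plan says.** The section on analysis of the primary endpoint sets the schedule: "Two interim analyses after inclusion of one third and two thirds of the patients, and one final analysis are planned". It gives the boundary levels as "0.00021 at the first analysis, 0.01202 at the second analysis and 0.04626 at the final analysis" and concludes: "The trial will be stopped early if the significance of the log-rank test is below these alpha values". No other condition is attached.

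The Data Safety Monitoring Board section says the board meets after each interim analysis, and then: "The Data and Safety Monitoring Board can propose to stop the study if interim statistical analyses reach significance". It may also propose a stop on safety grounds or because of published results.

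Three other places bear on the point:
- The Primary endpoint section takes time to surgery at 1 month as the endpoint and censors patients who die at the date of death.
- Under Study design: "Secondary objectives are to assess the effect of methylprednisolone on quality of life evolution, morbidity and mortality, and radiological evolution of the lesions". The Secondary endpoints section includes functional scales up to 6 months and survival at 6 months.
- The Follow-up section gives every patient 6 months of follow-up, without exception.

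**The concern.** Both sections govern the same event, a boundary crossing. One says the trial stops; the other says a board may suggest that it does. A board that saw a crossing together with an unfavourable pattern in deaths or function could not tell from the article whether it was free to advise continuing.

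The mandatory rule is also narrow. Its test statistic counts only operations within 1 month, and a death leaves the risk set as a censored observation. Avoiding or postponing surgery is a benefit only if patients are not worse off otherwise. The article itself calls surgery the gold standard, describes the population as fragile, and in its Discussion raises psychic and glycaemic risks of steroids. These are the outcomes that the literal rule leaves out of the stopping decision.

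**Working it through.** **1. The plan's own figures.** Inputs from the Study population section: "Our hypothesis is that 80% of the patients taking placebo will be operated on at 1 month", 60% with methylprednisolone, and "A total sample size of at least 202 patients (142 events) is required to achieve 90% power", "using a two-sided log-rank test with a 0.05 significance level assuming that the hazards are proportional".
- Hazard ratio = ln(0.20)/ln(0.40) = 1.756, as stated.
- Freedman events = (1.960 + 1.282)² × (2.756/0.756)² ≈ 140. The mean event rate is (0.80 + 0.60)/2 = 0.70, so 140/0.70 = 200 patients. This is close to the stated 142 and 202, and 202 × 0.70 = 141.4.
- O'Brien-Fleming-type spending at information fractions 1/3, 2/3 and 1 gives nominal two-sided levels of 0.000207, 0.01202 and 0.04626, which match the plan. The article calls them cumulative, but they are per-look levels, so using them as p-value thresholds is correct.

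**2. Chance of crossing.** Assumption: the looks fall at one third and two thirds of the events. The plan times them by inclusions.
- z bounds for the stated levels: 3.707, 2.512, 1.993.
- Drift for 142 events = ln(1.756) × √142/2 = 0.563 × 11.916/2 = 3.355.
- Look 1: mean z = 3.355 × √(1/3) = 1.937; P(z > 3.707) = 3.8%.
- Look 2: mean z = 3.355 × √(2/3) = 2.739; P(z > 2.512) ≈ 59%. The joint calculation over both looks gives 59.0%.
- With the drift set for exactly 90% fixed-sample power (1.960 + 1.282 = 3.242), the figures are 3.3% at look 1 and 55.4% by look 2.

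| True hazard ratio | Crossed by look 1 | Crossed by look 2 |
|---|---|---|
| 1.756 (planning value) | 3–4% | 55–59% |
| 1.4 | 0.5% | 19% |
| 1.0 (either direction) | 0.02% | 1.2% |

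**3. What a stop costs at 6 months.** Two thirds of 202 is about 135 patients; one third is about 67.
- Standard error ratio: √(202/135) = 1.22 at look 2; √(202/67) = 1.74 at look 1.
- Example with 6-month mortality assumed to be 10% (the article gives no rate): 95% half-width for a difference = 1.96 × √(2 × 0.1 × 0.9/n per arm) = 8.3 points at 202 patients, 10.1 at 135 and 14.4 at 67.

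**4. Would the full trial settle mortality?** Power for a doubling, two-sided 0.05, from Φ{(|p₁ − p₂|√n − 1.96√(2p̄(1 − p̄)))/√(p₁(1 − p₁) + p₂(1 − p₂))}, with n per arm and assumed base rates:

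| Base rate | 67 patients | 134 patients | 202 patients |
|---|---|---|---|
| 5% | 12% | 19% | 27% |
| 10% | 21% | 37% | 51% |
| 15% | 31% | 55% | 73% |
| 20% | 43% | 72% | 88% |

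**5. Type I error if the boundary is non-binding.** Under no effect, the stated levels give cumulative crossing probabilities of 0.0002, 0.0121 and 0.0500. A claim of efficacy requires a crossing at some look, so the chance of a false claim cannot exceed 0.05 whether or not the trial stops at the first crossing.

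**The case against.** The two sections can be read as complementary: the statistical section gives the numerical boundary, and the board section says who acts on it. The board has a stated safety role and includes a neurologist, an endocrinologist and a pharmacologist. Stopping on the primary endpoint with O'Brien-Fleming boundaries is a standard design, and the list of outcomes reviewed at each look usually belongs in a board charter. That reading is probably what was intended, and the absence of such a list is no fault of a condensed article. It does not remove the conflict, because the statistical section does not merely define a boundary; it states that the trial stops.

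A reader might go further and infer that an automatic stop would probably end the trial before its 6-month mortality and morbidity objectives could be answered. The documents do not support that:
- An early stop is more likely than not only if the planning effect is real. The Discussion says that effect was chosen from empirical experience.
- Nothing says follow-up ends with a stop. The 6-month schedule is unconditional, so recently included patients are part of the 135 and not a further loss.
- Mortality is a secondary endpoint without a sample-size basis. At base rates up to about 15%, the full 202 patients also fall short of 80% power for a doubling.

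The timing of the looks is a further limit. If an analysis were run at the inclusion count without waiting for recent patients to complete 1 month, fewer events would be available and the crossing probabilities would be lower.

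**Conclusion.** The conflict is real and should be corrected: one section mandates a stop and the other leaves it to a proposal. The mandatory version rests on a single 1-month statistic that does not count deaths against either arm. The choice of rule has practical weight: under the plan's own hypotheses, with looks at one third and two thirds of the events, the second look is crossed about 55–59% of the time. The consequence of a stop at that look is about one third fewer patients for the 6-month endpoints and standard errors about 1.22 times those planned. It is a loss of precision, and the 6-month objectives would not be lost altogether.

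**What to change.** Replace the mandatory sentence in the analysis of the primary endpoint with one rule that agrees with the board section. Crossing a boundary would permit the board to recommend stopping, after it has considered the available safety and functional data by arm at the same look. State that the efficacy boundary is non-binding and that the levels at later looks stay unchanged if the trial continues.

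As a clarification only, confirm that the 6-month follow-up still applies to patients already randomised if recruitment stops early.

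The cost is wording in the protocol and the board charter, with no change to the sample size or the boundaries. The downside is that recruitment may continue after a boundary has been crossed.

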#### Analysis of other criteria

Student’s *t* test or a Mann-Whitney test if necessary will be used to compare quantitative variables. Quantitative criteria evaluated several times during the monitoring will be compared with repeated measures analysis of variance (ANOVA) with two factors (time, group). For qualitative criteria, a chi^2^ test will be used. For all these analyses, adjustments can be made in case of heterogeneity at inclusion.

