#### Secondary endpoints

Secondary evaluation criteria are: quality of life assessed by the Short Form 12-item (SF12) scale [28] at 1, 3 and 6 months; time to surgical treatment during the first 6 months (censored criteria); rate of surgical treatment of the CSDH at 1, 3 and 6 months; functional scales: daily living (Instrumental Activities of Daily Living; IADL) [29], cognitive (Mini-Mental State Examination; MMSE) [30] and the modified Rankin Scale [31] at 1, 3 and 6 months; plasma sodium, potassium and fasting glucose at days 0, 7, 14 and 21 and at 1 month; occurrence of adverse events potentially related to methylprednisolone (electrolyte disorders: hypokalemia, metabolic alkalosis, sodium retention (edema), hypertension, congestive heart failure; endocrine and metabolic disorders: Cushing’s syndrome, adrenal insufficiency, glucose disorders (impaired glucose tolerance, diabetes); gastrointestinal disorders: ulcer, perforation, gastrointestinal tract hemorrhage; skin disorders: acne vulgaris, purpura, hematoma, hypertrichosis; neuropsychological disorders: euphoria, insomnia, agitation, confusion, depression; ophthalmological disorders such as glaucoma); survival at 6 months; radiological improvement, defined by reduction of maximal thickness of hematoma and reduction of midline shift evaluated at 1, 3 and 6 months.

Subgroup analyses of all study endpoints will also be performed in subacute (less than 4 weeks old) and chronic (more than 4 weeks old) CSDH, and in patients treated or not treated with anticoagulant or platelet antiaggregant therapy.

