### Description of the measures taken to reduce and prevent bias

#### Randomization

The randomization list will be prepared by the Biometrics Unit of the Clinical Investigation Centre Inserm 1414 of Rennes. Randomization will be stratified by center and equilibrated at a 1:1 ratio. After verification of selection criteria during the screening phase, the investigator will proceed to the randomization of the patient the day of baseline (D0). The investigator sends the order-processing request to the pharmacist of his center. The pharmacist attributes treatment to the patient according to their list in chronological order and informs the coordinating centre by faxing the completed order.

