#### Administration

The duration of treatment is 21 days. Capsules are administered orally in the morning, during breakfast. They will be dispensed by a nurse when patients may not be able to take capsules themselves. Prescription dosage is adapted according to the weight of the patient (approximately 1 mg/kg): three 16-mg capsules/day (patient <60 kg), four 16-mg capsules/day (patient 60–80 kg), five 16-mg capsules/day (patient >80 kg).

The treatment duration is supported by the pathophysiology of CSDH formation (inflammatory process supposed to be maximal at 2 to 3 weeks) [4, 8, 9, 11–19].

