#### Follow-up

Patients are followed up for a period of 6 months, and are evaluated at 1, 3 and 6 months. At days 0, 7, 14 and 21 and at the 1-month visit, plasma sodium, potassium and fasting glucose are measured. Fasting plasma cortisol at 8 a.m. is measured 2 days after the end of the treatment with corticosteroids (at day 23). Patients will undergo interval cerebral CT scans to evaluate their CSDH at the following intervals: screening visit, M1, M3 and M6 (Fig. 1). This biological surveillance allows the detection of any electrolyte or glycemic impairment that could occur with steroid treatment.

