#### Analysis of adverse events

Possible adverse events are coded according to the MedDRA classification and are the subject of a descriptive analysis.

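### The two-factor ANOVA planned for sodium, potassium and glucose has no term that estimates the on-treatment difference; a baseline-adjusted day 7 to 21 contrast would (minor)

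*Protocol article*

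**What the plan says.** The Secondary endpoints section of the protocol article lists "plasma sodium, potassium and fasting glucose at days 0, 7, 14 and 21 and at 1 month". The Follow-up section repeats the schedule: "At days 0, 7, 14 and 21 and at the 1-month visit, plasma sodium, potassium and fasting glucose are measured".

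Three statements place these samples relative to treatment:
- Randomization makes day 0 the baseline day: "the investigator will proceed to the randomization of the patient the day of baseline (D0").
- Administration fixes the length of the course: "The duration of treatment is 21 days".
- Follow-up says that morning cortisol "is measured 2 days after the end of the treatment with corticosteroids (at day 23"), so treatment ends on day 21.

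The analysis rule, under Analysis of other criteria, is general to all repeated quantitative outcomes: "Quantitative criteria evaluated several times during the monitoring will be compared with repeated measures analysis of variance (ANOVA) with two factors (time, group"). Baseline adjustment is optional: "For all these analyses, adjustments can be made in case of heterogeneity at inclusion". Adverse events have their own section: "Possible adverse events are coded according to the MedDRA classification and are the subject of a descriptive analysis".

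**The concern.** The ANOVA rule is generic. It is easier to apply to scales scored at 1, 3 and 6 months than to a laboratory series that starts before treatment and ends after it. The Follow-up section says the blood monitoring is there to pick up electrolyte and glucose disturbance from the steroid, so the quantity of interest is the between-arm difference while patients take the capsules.

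A two-factor repeated-measures ANOVA offers two between-arm terms, and neither is that quantity. The group main effect averages over visits at which little or no drug effect can be expected. The interaction asks whether the two profiles differ in shape. It has no direction or size, and it also reacts to recovery after treatment stops. The article does not say which term counts if the two disagree.

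At stake is the between-arm comparison of three safety-related laboratory values. Dilution here errs towards reassurance: a real shift could be reported as smaller than it is, or tested with less power than the data allow.

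**Working it through.** The documents give no effect size, SD, correlation or power for these laboratory values, so there is no figure of the plan's own to reproduce.

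**Inputs from the protocol article**
- Five samples: days 0, 7, 14, 21 and month 1 (Secondary endpoints, Follow-up).
- End of treatment: day 23 − 2 = day 21 (Follow-up), matching the 21-day course (Administration).
- Gap from end of treatment to month 1, counting a month as 30 days: 30 − 21 = 9 days.
- 101 patients per arm (Abstract).
- Significance level 0.05 (Statistical analysis), taken as two-sided.

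**Assumptions, not in the documents**
- The day 0 sample is taken before the first dose. This is inferred from day 0 being baseline.
- A constant difference d at days 7, 14 and 21, with d = 0.3 SD.
- Equal correlation r between any two samples, r = 0.3, 0.5 or 0.7.
- Complete, balanced data.

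**Step 1: what the group main effect estimates.** With balanced data it is the unweighted mean of the per-visit differences.

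| Month-1 difference | Day 0 as an outcome | Day 0 left out of the outcomes |
|---|---|---|
| none | (0+d+d+d+0)/5 = 0.60d | 3d/4 = 0.75d |
| half persists | 3.5d/5 = 0.70d | 3.5d/4 = 0.875d |
| fully persists | 4d/5 = 0.80d | 4d/4 = 1.00d |
| half-size reversal | 2.5d/5 = 0.50d | 2.5d/4 = 0.625d |

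Randomization makes the expected day 0 difference zero. With day 0 kept as an outcome, the group term therefore falls short of d unless the month-1 difference is larger than the on-treatment one.

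**Step 2: power for the profile (0, d, d, d, 0).** For a mean contrast, z = effect × √(101/(2V)) and power = Φ(z − 1.96), with SD set to 1.

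- Group main effect: effect 0.6 × 0.3 = 0.18; V = (1+4r)/5 = 0.44 / 0.60 / 0.76; z = 1.93 / 1.65 / 1.47.
- Interaction: noncentrality (101/2) × d² × S/(1−r), where S = 2 × 0.6² + 3 × 0.4² = 1.2. This gives 5.454/(1−r) = 7.79 / 10.91 / 18.18 on 4 and 800 degrees of freedom.
- Mean of days 7, 14 and 21, unadjusted: V = (1+2r)/3 = 0.533 / 0.667 / 0.800; z = 2.92 / 2.61 / 2.38.
- The same mean adjusted for day 0: V = (1+2r)/3 − r² = 0.443 / 0.417 / 0.310; z = 3.20 / 3.30 / 3.83.

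| Analysis | r = 0.3 | r = 0.5 | r = 0.7 |
|---|---|---|---|
| Group main effect, five visits | 49% | 38% | 31% |
| Group-by-time interaction | 59% | 76% | 94% |
| Days 7–21 mean, unadjusted | 83% | 74% | 66% |
| Days 7–21 mean, adjusted for day 0 | 89% | 91% | 97% |

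At d = 0.4 SD and r = 0.5 the four figures are 60%, 96%, 94% and 99%.

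**Step 3: reading the table.** The group main effect is the weakest choice throughout. The interaction is much better, and at r = 0.5 and 0.7 it beats the unadjusted on-treatment mean. The advantage of the proposed contrast over the interaction at those correlations therefore comes from always using the day 0 value. It shrinks as correlation or effect size grows.

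**The case against.** The strongest objection is that the article nowhere says visits are averaged or that the group main effect is the test. A two-factor repeated-measures ANOVA ordinarily includes the group-by-time interaction, which reacts to a difference that appears on treatment and fades afterwards. The choice of term and the handling of day 0 are often left to an analysis plan, and none is shown here. This stands, and it limits the point: the dilution is conditional on which term is used.

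A reader might infer that the plan will report 60% of the true effect. The documents do not support that. The figure needs day 0 kept as an outcome, no difference at month 1 and balanced data, and none of these is stated. Other plausible cases run from 0.50 to 1.00.

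A reader might also infer that the trial will understate steroid harm in general. That does not follow. Electrolyte and glucose disorders are also listed as adverse events, and adverse events are analysed descriptively with no averaging over visits. Monitoring of individual patients does not depend on an ANOVA result either.

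The objection does not remove the remaining problem. The method is stated for this series, neither of its between-arm terms estimates the on-treatment difference, and baseline adjustment is triggered only by observed imbalance. Visit-level contrasts are not excluded, but none is specified.

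**Conclusion.** The point holds in conditional form, as a minor one. If the group main effect over all five samples is used, it is diluted to 0.60 of the on-treatment difference with no month-1 effect and to 0.80 with full persistence. If day 0 is left out and month 1 shows no effect, the ratio is 0.75. If the interaction is used, the pattern is likely to be detected, but without an on-treatment effect size, and with less power than the adjusted contrast by about 30, 15 and 3 percentage points at correlations 0.3, 0.5 and 0.7 (d = 0.3 SD).

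The multipliers follow from the visit schedule, a pre-dose day 0 sample and balanced data. The power figures rest on assumed effect size and correlation and show order of magnitude only. The consequence is a laboratory comparison that may be understated or inefficient. The primary endpoint and the adverse event reporting are unaffected.

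**What to change.** For plasma sodium, potassium and fasting glucose, prespecify the between-arm contrast as the mean of days 7, 14 and 21, with the day 0 value always included as a covariate, for example in a mixed model. Report month 1 separately as post-treatment recovery, outside the averaged effect. The generic ANOVA sentence can stay for the other repeated outcomes.

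This takes one sentence of analysis wording and uses only samples already scheduled. The only downside is one extra reported contrast, for month 1.

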#### Primary endpoint

The primary evaluation criterion is the delay of occurrence of surgical treatment (censored criteria) of the CSDH at 1 month. One month has been chosen for assessing the primary endpoint because most surgical interventions, if needed, are expected to occur during the first month following the diagnosis of CSDH. Patients who are nonevaluable for the primary endpoint (death, loss to follow-up, etc.) will be censored at the date of death or the latest news.

Criteria for recourse to surgery are (one is sufficient): lack of clinical improvement at 1 month, immediate or delayed clinical deterioration, appearance of radiological signs of severity (midline shift >5 mm, uncal transtentorial herniation).

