#### Baseline data collection

The following information is collected before initiation of the treatment:

Patients’ characteristics: sex, age, weight, height, major medical history (including chronic alcoholism), ongoing medications affecting hemostasis (anticoagulants and platelet antiaggregants), and symptoms that led to the diagnosis of CSDH (persistent headache, repeated falls, balance disorders, attention and memory disorders, muscular weakness, motor or sensitivity disorders).

The clinical assessment includes: blood pressure measurement, neurological examination (Glasgow Coma Scale (GCS) score, diameter and symmetry of the pupils, presence of a focal neurological deficit), functional scales (modified Rankin Scale, IADL and MMSE assessments, quality of life (SF12 scale) and comprehensive review of the overall clinical assessment score with the ASA (American Society of Anesthesiologists).

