### Statistical analysis

Statistical analysis will be performed on all evaluated patients (intention-to-treat analysis in the methodology/biometrics unit of the Clinical Investigation Centre Inserm 1414 of Rennes. The statistical significance will be considered to be *p* values < 0.05 for all analysis.

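### Repeated secondary scales get a time-and-group ANOVA with adjustment only if imbalance is seen, so baseline value and center are unused by default and adjustment depends on the data

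*Protocol article*

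**What the plan says.** All references are to the protocol article.

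- **Model** (Analysis of other criteria): "Quantitative criteria evaluated several times during the monitoring will be compared with repeated measures analysis of variance (ANOVA) with two factors (time, group").
- **Adjustment** (same section): "For all these analyses, adjustments can be made in case of heterogeneity at inclusion". The wording is permissive. It names no covariate, no test of imbalance and no threshold, and it covers every analysis in that section.
- **Baselines recorded** (Baseline data collection): "functional scales (modified Rankin Scale, IADL and MMSE assessments, quality of life (SF12 scale").
- **Endpoint visits** (Secondary endpoints): "quality of life assessed by the Short Form 12-item (SF12) scale [28] at 1, 3 and 6 months"; the functional scales follow the same visits. The laboratory values are listed differently, with day 0 among the time points: "plasma sodium, potassium and fasting glucose at days 0, 7, 14 and 21 and at 1 month".
- **Stratification** (Randomization): by center, at a 1:1 ratio.
- **Analysis set** (Statistical analysis): "Statistical analysis will be performed on all evaluated patients (intention-to-treat analysis").
- **Incomplete follow-up** (Primary endpoint): "Patients who are nonevaluable for the primary endpoint (death, loss to follow-up, etc.) will be censored at the date of death or the latest news". This rule is for the primary endpoint only.

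**The concern.** A baseline score usually predicts the later score on the same scale. Adjusting for it makes the arm comparison more precise whether or not the arms happen to differ at entry. The stated rule ties adjustment to observed imbalance instead. When the arms look alike, the precision is given up. When they do not, someone must decide after seeing the data what counts as heterogeneity and which variables to enter, and that choice can move the p-value.

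Quality of life is one of the stated secondary objectives, and function bears on whether avoiding surgery benefits these patients. Both would be estimated less precisely than the collected data allow, with an analyst's choice left open.

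A further issue depends on how the ANOVA is run. In its classical form it needs a value at every visit. Follow-up lasts 6 months in a population the Background describes as often fragile, and the article itself foresees death and loss to follow-up.

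**Working it through.** The article gives no effect size, correlation or missingness rate for these endpoints, so there is no figure of the plan to reproduce. From the documents I take 202 patients (101 per arm) and three follow-up visits. The correlation r between baseline and follow-up, and the missingness m per visit, are assumptions shown over a range.

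**1. Precision at a single visit** (common variance set to 1)

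- Follow-up score alone: variance 1.
- Change from baseline: 2(1 − r).
- Baseline-adjusted: 1 − r².

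| r | Follow-up | Change | Adjusted | Cut vs follow-up | Cut vs change |
|---|---|---|---|---|---|
| 0.5 | 1 | 1.00 | 0.75 | 25% | 25% |
| 0.7 | 1 | 0.60 | 0.51 | 49% | 15% |

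The last column is 1 − (1 + r)/2. It covers the case where baseline is a level of the time factor and the arms are compared on change.

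**2. Precision for the mean of three visits** (equal correlation r between all occasions)

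The unadjusted variance is (1 + 2r)/3 and the adjusted variance is (1 + 2r)/3 − r². Take an effect that the adjusted analysis detects with 90% power at 101 per arm, two-sided 0.05:

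| r | Unadjusted | Adjusted | Ratio | Power without baseline |
|---|---|---|---|---|
| 0.3 | 0.533 | 0.443 | 0.83 | 84% |
| 0.5 | 0.667 | 0.417 | 0.63 | 73% |
| 0.7 | 0.800 | 0.310 | 0.39 | 52% |

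If baseline were a fourth time level and the group main effect were read, the effect would shrink by the factor 3/4, because no treatment effect can exist at baseline. Power would be 65%, 51% and 34%.

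**3. The adjustment rule**

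The standardised baseline difference b and outcome difference y were simulated under no treatment effect with correlation r (400,000 draws, one visit). The unadjusted statistic is y and the adjusted one is (y − r·b)/√(1 − r²). Nominal type I error is 0.05.

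| Rule | r = 0.3 | r = 0.5 | r = 0.7 |
|---|---|---|---|
| Always adjust | 0.050 | 0.050 | 0.050 |
| Adjust only if baseline p < 0.05 | 0.048 | 0.043 | 0.036 |
| Free choice of either result | 0.064 | 0.073 | 0.083 |
| Unadjusted test, given an imbalance of 1.5 to 1.96 standard errors that misses the trigger | 0.07 | 0.10 | 0.14 |

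**4. Patients lost, if the ANOVA is complete-case**

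The share missing at least one of three visits is 1 − (1 − m)³.

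- m = 5%: 1 − 0.95³ = 14.3%, leaving about 173 of 202.
- m = 10%: 1 − 0.90³ = 27.1%, leaving about 147 of 202.

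Under monotone dropout the loss is the dropout rate itself: 10% by month 6 leaves about 182 of 202.

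**The case against.** The strongest reply is that much depends on an implementation the article does not describe, and that a condensed article may leave such detail to an SAP that is not shown. Several stronger readings fail on this ground.

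- **That the plan discards incomplete patients.** No complete-case rule is stated, and the analysis set carries an intention-to-treat label. The loss in step 4 is a consequence of the classical method, not of a sentence in the text. How missing values are handled is properly SAP material.
- **That the effect is averaged over time.** A two-factor repeated-measures ANOVA normally includes the group-by-time interaction, and the article does not say that only the main effect will be read. The 65%, 51% and 34% in step 2 apply only if it is.
- **That baselines are ignored altogether.** Day 0 is listed for the laboratory values, baseline is not excluded from the time factor for the scales, and adjustment is permitted. The supportable wording is unused by default.
- **That type I error is inflated.** Under a strict p < 0.05 trigger it is at or below nominal overall. The rise to about 0.08 needs a free choice between results, which the article does not grant in so many words.
- **That Rankin goes into the ANOVA.** The article has one rule for quantitative and another for qualitative criteria and does not assign this ordinal scale to either.

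What remains does not rest on absent detail. The article names a model with two factors and states a rule that makes adjustment depend on observed imbalance. Treating baseline as a time level does not close the gap either: the comparison on change still has more variance than the baseline-adjusted one (step 1).

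**Conclusion.** The point holds as a better method available at no cost, not as an error in a stated figure. By default the model leaves out the baseline values of SF12, IADL and MMSE and the stratification factor, and the decision to adjust is data-dependent.

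The gain in single-visit variance from fixed baseline adjustment is 25% to 49% against follow-up scores, or 25% to 15% against change from baseline, for r from 0.5 to 0.7. Type I error under the adjustment rule lies between about 0.036 and 0.083, depending on r (0.3 to 0.7) and on how the rule is applied; fixed adjustment holds it at 0.05. The loss of 14% to 27% of patients is conditional twice: on a complete-case ANOVA and on 5% to 10% independent missingness per visit.

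The correlations and missingness rates are all assumed. A reader might infer that the trial's main result is in doubt. It is not: the log-rank comparison of time to surgery uses neither this model nor this adjustment rule.

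**What to change.** 1. Replace the two-factor ANOVA with a likelihood-based mixed model for repeated measures on all randomised patients with any follow-up value of the scale. Pre-specify arm, visit, arm-by-visit, baseline value of that scale and center, and report the arm contrast at each visit. The article does not give the number of centers; if some are small, state beforehand how they will be handled.
2. Delete the sentence that permits adjustment for heterogeneity. Fix the covariates before the treatment code is open to the analyst. Because that sentence also covers the section's other tests, each of those should have a fixed covariate list or be declared unadjusted.
3. State the limits. The mixed model relies on data being missing at random, and it does not resolve scores that are undefined because the patient has died.
4. Optional: a proportional-odds model with baseline Rankin as covariate for the modified Rankin Scale.

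The cost is wording in the protocol or SAP and standard software. The baseline values are already collected and center is known for every patient, so no new data are needed.
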